# Effectiveness of an online education program for asthma patients in general practice: study protocol for a cluster randomized controlled trial

**DOI:** 10.1186/s12890-022-02217-2

**Published:** 2022-12-01

**Keywords:** Asthma, Patient education, Self-management, Asthma knowledge, Digital intervention, Cluster randomized controlled trial, Primary care

## Abstract

**Background:**

Asthma education programs (AEPs) have been shown to increase quality of life and reduce emergency treatments and hospital admissions. Despite the proven benefits, only a minority of asthma patients attend such programs. To increase the number of educated patients, an online education program (electronic AEP, eAEP) for asthma patients has been developed. The present study aims to investigate the effectiveness of the eAEP in terms of asthma knowledge, asthma control and emergency treatments in general practice settings.

**Methods:**

This is a cluster randomized controlled trial including 100 patients with bronchial asthma from 20 general practices in Bavaria, Germany. General practices will be randomly assigned to either the intervention or control group. Patients in the intervention group will receive access to the eAEP and instructions to complete this program within two weeks. Patients in the control group will receive usual care including a referral to face-to-face AEP (fAEP) by a certified primary care physician or a pulmonologist according to guideline recommendations. Furthermore, patients of both the intervention and control groups will be invited to a follow-up consultation in their general practice after completion of the eAEP and fAEP (three weeks and twelve weeks after study inclusion, respectively) to discuss any open issues. Outcomes for both groups will be assessed at baseline (t_0_), after two weeks (t_1_), three months (t_2_) and six months (t_3_). The primary outcome is the comparison of asthma knowledge gain between intervention and control groups after completion of the eAEP (two weeks after study inclusion) and fAEP (twelve weeks after study inclusion), respectively. Secondary outcomes include asthma control, frequency of emergency treatments, patient autonomy as well as attitudes towards asthma medication.

**Discussion:**

The results of the present trial will provide knowledge about the effectiveness of an online education program for asthma patients compared to usual care in primary care.

**Trial registration:**

German Clinical Trials Register (DRKS), DRKS00028805. Registered 22 April 2022.

**Supplementary Information:**

The online version contains supplementary material available at 10.1186/s12890-022-02217-2.

## Background

Bronchial asthma is an inflammatory respiratory disease affecting both children and adults. Symptoms are periodic and often vary over the course of day and night. Common asthma symptoms include coughing, wheezing, shortness of breath and chest tightness [1]. In most cases, asthma requires long-term management in order to achieve asthma control, reduce exacerbations as well as the risk of asthma-related death and persistent airflow limitation [1]. Essential components of therapy recommended by guidelines include appropriate assessment and monitoring of asthma, drug therapy, as well as patient education [1].

Patient education is a substantial part of non-drug therapy and provides knowledge and skills in order to improve patient self-management [1, 2]. Structured asthma education programs (AEPs) address essential topics such as correct inhaler use, self-monitoring of symptoms, peak flow assessment, a written action plan in case of asthma worsening and the importance of regular review by health care providers. Evidence has shown that AEPs advance health-related outcomes encompassing an improvement in quality of life, and reductions in hospital admissions and emergency treatments [3]. In Germany, AEPs need to be accredited in order to receive reimbursement for patient education in practices. In primary care, AEPs are predominantly provided in presence by pulmonologists or general practitioners (GPs) certified for conducting AEPs.

However, despite the nationwide existence of several structured patient education programs, only few patients with asthma participate in such programs [3, 4]. AEPs often entail barriers for patients as patients must be willing to invest time, practices offering AEPs involve long journeys or include limited capacity in scheduling. Additionally, COVID-19 has generated a considerable reduction in face-to-face appointments offered [5].

Due to improved accessibility, online formats might lower the threshold for participation in education programs and thereby increase participation rates. As a consequence, an online education program (electronic AEP, eAEP) for asthma patients was developed based on the face-to-face AEP (fAEP) of the Bad Reichenhall clinic in Germany, a center for inpatient pulmonary rehabilitation. The online format allows flexible use via PC, notebook or smartphone and enables patients to acquire knowledge on asthma basics, drug therapy as well as self-management.

The eAEP has already been evaluated in two proof-of-concept studies [6, 7]. It was first evaluated in 2018 in a randomized controlled pilot study conducted in the aforementioned pulmonary rehabilitation center in Bad Reichenhall, Germany. This study showed that a combination of eAEP and conventional AEP resulted in a significantly higher asthma knowledge compared to patients only attending the fAEP [6]. However, as GPs are of substantial importance in the management of patients with asthma, the eAEP could prove particularly helpful in primary care. Since the significance of the results of a rehabilitation clinic is limited when transferring to primary care, a single-arm pilot study was conducted in 12 general practices in Upper Bavaria, Germany, in 2019 [7]. After completion of the eAEP, patients received a questionnaire sent by mail consisting of an evaluation of the online program and an asthma knowledge test (AKT) [8]. The eAEP was well accepted and evaluated positively by patients of primary care. After completion of the eAEP a doubling of the asthma knowledge score in the AKT was observed (corresponding scale: 0 to 54 points) [7]. Consequently, the eAEP also proved to be feasible in primary care.

Nonetheless, the effectiveness of the eAEP at the level of general practice on asthma knowledge as well as its effect on additional clinical outcomes remain uncertain.

Moreover, asthma as a chronic disease commonly requires long-term management as well as self-management skills. As patients’ willingness and ability to engage in self-management may vary depending on multiple factors such as literacy, attitudes towards asthma and medications and desire for autonomy, patients’ individual expectations and beliefs should be highlighted [1]. We assume that patient education leads to higher preference for participation in shared decision making and increased medication adherence.

### Aims and Outcomes

This cluster randomized controlled trial (cRCT) aims to investigate the effectiveness of the eAEP compared to usual care in terms of 1) asthma knowledge, 2) asthma control, and 3) emergency treatments including the following endpoints:Baseline-adjusted difference in the number of correctly answered questions in the AKT [8] between intervention and control groupsprimary endpoint: after the eAEP (two weeks after study inclusion) and fAEP (twelve weeks after study inclusion), respectively.secondary endpoint: three months after the eAEP (three months after study inclusion) and fAEP (six months after study inclusion), respectively.secondary endpoint: at the end of the study (six-month follow-up).

Further secondary endpoints include:2)Baseline-adjusted difference in the total sum score obtained in the asthma control test (ACT) [9] between intervention and control groupsthree months after the eAEP (three months after study inclusion) and fAEP (six months after study inclusion), respectively.at the end of the study (six-month follow-up).3)Difference in frequency of emergency treatments (inpatient and outpatient treatments of asthma) between intervention and control groups at six months.

This trial further examines the relation between asthma knowledge and 4) patient autonomy as well as 5) attitudes towards asthma medication including the following endpoints:4)Correlation between the total sum score achieved in the autonomy preference index (API) [10] at the time point baseline assessment and the change in correctly answered questions in the AKT after the eAEP and fAEP, respectively.5)Correlation between the total sum score obtained in the questionnaire on attitudes towards asthma medication at the time point baseline assessment and the change in correctly answered questions in the AKT after the eAEP and fAEP, respectively.

## Methods/Design

### Study design

This study will be conducted as multicentre cRCT including 100 patients with bronchial asthma from 20 general practices in Bavaria, Germany. General practices will be randomly assigned to either the intervention or control group. Therefore, patients in one practice will receive the same treatment. Cluster randomization is a common procedure in health services research in primary care in order to prevent contamination of care [11–13].

All patients with asthma will be informed about the study and informed consent will be obtained. Patients from general practices in the intervention group will receive free access to the eAEP and will be asked to complete the eAEP within the following two weeks. Patients from general practices in the control group will receive usual care including a referral to a practice of pulmonology or a certified general practice for structured fAEP. Patients will be required to attend the fAEP within twelve weeks. As part of the baseline assessment, patients will complete a questionnaire including questions on their asthma characteristics, current medication and emergency treatments within the past six months. In addition, a structured questionnaire including the AKT, ACT and API as well as questions on patients’ attitude towards asthma medication will be handed out (further details on the questionnaires are depicted in the section ‘Measurements’). Furthermore, current lung function parameters will be extracted from patient chart or spirometry will be performed to assess lung function in terms of FEV_1_ and FEV_1_/FVC. Two weeks after study enrolment, all patients will receive the AKT by mail to complete the questionnaire again. After completion of the eAEP (three weeks after inclusion) or fAEP (twelve weeks after inclusion) patients will attend a follow-up consultation in the general practice in order to review the asthma knowledge gain as well as to discuss any open issues. In order to ensure adherence to the second appointment, all patients will be contacted via phone by an employee of the Institute of General Practice and Health Services Research at the Technical University of Munich. As part of a follow-up, patients in both groups will be contacted again by mail after three as well as six months and asked to complete a questionnaire comprising the AKT, ACT, API as well as questions on the attitude towards asthma medication. In addition, at the six-month follow-up, participants will be inquired to answer questions about emergency treatments. A detailed overview of the course of the present trial can be seen in Fig. 1.

**Fig. 1 Fig1:**
[figure not shown]
Overview of the course of the study. AKT implies asthma knowledge test; ACT, asthma control test; API, autonomy preference index; NASA, national asthma education program for adult asthmatics; t_0_, time point 0 (baseline assessment); t_1_, time point 1 (two weeks after study inclusion); t_2_, time point 2 (three-month follow-up); t_3_, time point 3 (six-month follow-up)

### Recruitment and Randomization

In this study, 20 general practices in Bavaria, Germany, will be included. Practices will be recruited by contacting GP’s of the institute’s teaching practices network and of the bavarian practice-based research network (BayFoNet). The Institute of General Practice and Family Medicine, Ludwig-Maximilians-University in Munich (LMU Munich) and the Institute of General Practice, Friedrich-Alexander University Erlangen-Nürnberg (FAU), which are also part of BayFoNet, will support recruitment of general practices. The allocation of the general practices to the intervention or control group will be conducted by a statistician [name] of the study team, whom is not involved in the study conduct. For this purpose, a randomization sequence will be generated using the program R (The R Foundation for Statistical Computing, Vienna, Austria). The allocation ratio of intervention to control group at 1:1, no stratification, and randomly varying block sizes will be documented in advance. The randomization list will be prepared and retained by the statistician. After inclusion of general practices in the study, practices will be consecutively added to the randomization list by the statistician and assigned an appropriate sequential number. The statistician will report the corresponding classification of the practice into the study arm to the study coordinator.

After allocation of the general practice to the intervention or control group, patients will be consecutively recruited by the participating general practice. Patients will not be blinded with regard to the intervention. The practice team will check the inclusion and exclusion criteria. Furthermore, the attending physician will inform patients about the study. If patients may be eligible for the study but are unwilling to participate, age, sex, and the reason for non-participation will be documented anonymously using a non-responder list. Thus, it is possible to conduct a non-responder analysis to assess acceptance of the eAEP offer as well as fAEP.

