#### Control Group (usual care)

Patients from general practices in the control group will receive care as usual according to guideline recommendations. This encompasses either a referral to a pulmonary practice for structured fAEP or a structured fAEP in a certified general practice. Patients will be asked to attend the fAEP within twelve weeks. Furthermore, patients in the control group will also receive a peak flow meter and an asthma diary in advance.

Twelve weeks after study enrolment, patients in the control group will visit the general practice again to discuss remaining questions as well as to test patients’ asthma knowledge on the basis of the “physician-patient-appointment” questionnaire. At the end of the study, patients of the control group will also receive access to the eAEP.

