### Statistics

#### Sample size estimation

The power calculation is based on the results of the pilot study conducted in 2019 [7] using a two-sample t-test: An average difference of 22 points in the AKT (corresponding scale ranges from 0 to 54 points) was observed between baseline measurement and after completion of the eAEP (two weeks after study inclusion). A more conservative approach of an average difference of 20 points is applied for planning the current study. As the pilot study did not include a control group, an average asthma knowledge gain of 5 points was estimated for the control group of the present study. This estimation is based on the assumption, that about 25% of the patients in the control group will attend a fAEP and therefore achieve an average knowledge gain of maximum 20 points [3, 4]. The remaining 75% of the patients are expected to reach an average knowledge gain of 0 points. This results in 0.25 x 20 points + 0.75 x 0 points = 5 points. In order to include all available data in statistical analyses as well as to prevent an attrition bias, the intention-to-treat principle is applied in this study with an expected drop-out rate of 20%. Performing a worst-case-analysis [15], it is assumed that drop-out patients in the intervention group achieve an average knowledge gain of 0 points. Accordingly, an average asthma knowledge gain of 16 points is expected in the intervention group (0.80 x 20 points + 0.20 x 0 points). Considering a worst-case-analysis, the average asthma knowledge gain is assumed to double for drop-out patients in the control group resulting in an average knowledge gain of 6 points (0.80 x 5 points + 0.20 x 10 points). The sample size estimation is based on a standard deviation of 15. Using a two-sample t-test and a two-sided 5 % significance level, the number of patients per group is 36 to achieve a power of 80 %. Due to cluster randomization, the number of patients has to be increased by the design effect (DE). The sample size estimation of the current study is based on an intracluster correlation coefficient (ICC) of 0.10 [16], a mean cluster size of 5 and a resultant DE of 1.4 (calculation based on [13]). Regarding the primary outcome asthma knowledge gain, the number of patients required is therefore 100 (2 x 36 x 1.4 ≈ 100).

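### The list of patients who decline the study measures willingness to join the study, so it cannot by itself show acceptance of the eAEP or, especially, of the fAEP

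*Protocol article*

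**What the plan says.** Under Recruitment and Randomization, practices are allocated first and patients are recruited afterwards: "After allocation of the general practice to the intervention or control group, patients will be consecutively recruited by the participating general practice". The same section sets up the non-responder list: "If patients may be eligible for the study but are unwilling to participate, age, sex, and the reason for non-participation will be documented anonymously". It then draws the conclusion at issue: "Thus, it is possible to conduct a non-responder analysis to assess acceptance of the eAEP offer as well as fAEP".

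Three other places bear on this:

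- Control Group (usual care): "Patients from general practices in the control group will receive care as usual according to guideline recommendations". This care includes the fAEP, by referral to a pulmonary practice or in a certified general practice.
- Sample size estimation: the plan expects that "about 25% of the patients in the control group will attend a fAEP", and adds: "The remaining 75% of the patients are expected to reach an average knowledge gain of 0 points".
- Background: the motive for the online programme is that "online formats might lower the threshold for participation in education programs and thereby increase participation rates".

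The article gives no acceptance rate, numerator or denominator, and acceptance is not among the endpoints under Aims and Outcomes.

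**The concern.** The inference from the list to acceptance does not follow. Joining the study means giving consent, filling in repeated questionnaires, taking a phone call and returning for a GP appointment. A patient may decline all of that and still be willing to take the programme. Equally, a patient may consent and never take it.

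The gap is widest for the fAEP. A patient in a control practice who declines the study remains entitled to the fAEP as ordinary care. A patient who enrols has not thereby attended, and on the plan's own assumption most will not. Controls also receive eAEP access at the end of the study, so enrolment in a control practice can reflect interest in something other than the fAEP.

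What is at stake is limited but relevant to the trial's rationale, which is that few patients attend face-to-face programmes and an online format might raise participation. Refusal shares by arm would be a poor guide to that contrast. The Discussion itself accepts that allocation may affect recruitment, and that effect would be mixed in.

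**Working it through.** **The plan's figures.** The expected control gain reproduces: 0.25 × 20 + 0.75 × 0 = 5 points. So does the sample size: 36 per group with a 10-point difference (16 − 6) and SD 15 by the normal approximation; design effect 1 + (5 − 1) × 0.10 = 1.4; and 2 × 36 × 1.4 = 100.8, stated as about 100. With 20 practices allocated 1:1 and a mean of 5 patients each, that is about 50 enrolled patients per arm. The article states no acceptance figure to reproduce.

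**Enrolled controls.** Attending a fAEP: 50 × 0.25 = 12.5. Not attending: 50 × 0.75 = 37.5. None of these 37 or 38 patients would be on the non-responder list, because all of them consented.

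**What follows if one minus refusal were taken as acceptance.** This reading is an assumption; the article does not state it. Let r be the share of eligible patients who decline the study and q the fAEP attendance among decliners. Neither is in the document, so both are varied.

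- Acceptance implied by the list: 1 − r
- fAEP uptake among all eligible patients: 0.25 × (1 − r) + r × q

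| r | 1 − r | uptake, q = 25% | ratio | uptake, q = 100% | ratio |
|---|---|---|---|---|---|
| 10% | 90% | 25% | 3.6 | 32.5% | 2.77 |
| 20% | 80% | 25% | 3.2 | 40% | 2.0 |
| 30% | 70% | 25% | 2.8 | 47.5% | 1.47 |
| 40% | 60% | 25% | 2.4 | 55% | 1.09 |
| 50% | 50% | 25% | 2.0 | 62.5% | 0.8 |

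If no decliner attended (q = 0), the ratio would be 1/0.25 = 4.0 at every r. That is the extreme case, and it sits badly with the fAEP being usual care.

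**When the direction changes.** The list overstates uptake while 0.75 × (1 − r) > r × q. With q = 100% this needs r < 0.75/1.75 = 43%. With q = 25% it needs r < 0.75/1.00 = 75%.

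**The eAEP.** The article gives no completion figure and says website use is not logged. If the 20% expected drop-outs are taken as non-users (an assumption), the ratio among enrolled patients is 1/0.80 = 1.25. Otherwise it is unknown.

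**The case against.** The strongest reply is that the article only calls such an analysis possible. It defines no measure, and filling in an optional descriptive analysis is ordinary work for an analysis plan. That stands as far as the missing definition goes. It does not rescue the inference that is stated, which names a data source that does not fit the purpose.

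A second reply is that acceptance of an offer can mean willingness at the time it is made, and that recorded reasons separate refusals of the programme from refusals of the research. This is partly right for the eAEP. For the fAEP it falls short: agreeing to the study is not agreeing to attend, and reasons exist only for listed patients, so enrolled non-attenders stay invisible.

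Third, uptake may be captured elsewhere. The primary model includes time since eAEP/fAEP, which implies that programme dates are recorded, and controls have a GP review at twelve weeks on a form that is not shown. This is fair and makes the fix easier, but the article does not tie acceptance to those data.

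A reader might also infer that the arms are treated unequally, because someone who dislikes the fAEP can enrol as a control while someone who dislikes the online course declines. The document gives weak support for this. Both arms are asked to take a programme (Study design; Control Group), and an unwilling patient could enrol or decline in either.

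**Conclusion.** The point holds as a mismatch between data source and purpose. The list describes who declines the study; it does not measure acceptance of either programme, and the misfit is greatest for the fAEP. On the plan's 25% attendance assumption, about 37 of 50 enrolled controls would be non-attenders whom the list cannot show.

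A reader might go further and conclude that enrolled patients who never take the programme are counted as accepters, so that fAEP acceptance is grossly overstated. The document does not support this: no rule counts them that way and no acceptance figure is given. The 3.6- to 2.0-fold range applies only if acceptance is read as one minus refusal, with r assumed at 10% to 50%, q assumed at 25%, and the 25% for enrolled controls taken from planning. The sign is not guaranteed either. It can reverse above about 43% refusal if every decliner attends. For the eAEP the overstatement is much smaller on the drop-out assumption, or unknown.

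The matter is minor. No primary or secondary endpoint, test or sample size depends on it.

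**What to change.** 1. In Recruitment and Randomization, state that the non-responder list describes study participation and representativeness by arm, with each reason coded as programme-related or study-related.
2. Report programme uptake separately, by arm, among enrolled patients. As a supplement, report it among all eligible patients approached (enrolled plus listed), noting that attendance among decliners is not observed.
3. Take uptake from one yes/no item on the existing GP review form and on the existing three-month mailed questionnaire, in both arms. The mailed questions on fAEP attendance are at present described for the intervention group only, so controls need the item added.
4. Report missing uptake as unknown, with best-case and worst-case bounds, rather than as not taken. In the pilot only 60% attended the review appointment. At that rate, with no mailed answer to fill the gap, 50 × 0.40 = 20 patients per arm would be unknown and the bounds would be 40 percentage points apart. Coding them as not taken would present the lower bound as the estimate.

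The cost is a reworded sentence, a reason code and one item on existing forms, with no extra patients or visits. The downside is that reported acceptance will probably be lower, mainly for the fAEP, and that eAEP uptake rests on self-report because website use is not logged.
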